# A good beginning: study protocol for a group-randomized trial to investigate the effects of sit-to-stand desks on academic performance and sedentary time in primary education

**DOI:** 10.1186/s12889-019-8135-9

**Published:** 2020-01-15

**Keywords:** Sedentary behavior, Primary school, Children, Health, Academic performance, Cognition, Quality of life, Intervention, Sit-to-stand desks

## Abstract

**Background:**

Sedentary behavior is associated with health risks and academic under-achievement in children. Still, children spend a large part of their waking hours sitting at a desk at school. Recent short-term studies demonstrated the potential of sit-to-stand desks to reduce sitting time in primary education. The program of “A Good Beginning” was conceived to assess the long-term effects of sit-to-stand desks on sitting time in primary education, and to examine how sit-to-stand desks versus regular desks relate to academic performance, and measures of executive functioning, health and wellbeing. The present paper describes the design of this group-randomized trial, which started in 2017 and will be completed in 2019.

**Methods:**

Children of two grade-three groups (age 8–9) following regular primary education in Leiden, The Netherlands, were recruited. A coin toss determined which group is the experimental group; the other group is the control group. All children in the experimental group received sit-to-stand desks. They are invited and motivated to reduce sedentary time at school, however, it is their own choice to sit or stand. Children in the control group use regular desks. Otherwise, both groups receive regular treatment. Outcomes are assessed at baseline (T0) and at five follow-up sessions (T1-T5) alternately in winter and summer seasons over three academic years. Primary outcome measures are academic performance, and the proportion of sitting time at school, measured with a 3D accelerometer. Secondary outcome measures are a number of measures related to executive functioning (e.g., N-back task for working memory), health (e.g., height and weight for BMI), and wellbeing (e.g., KIDSCREEN-52 for Quality of Life).

**Discussion:**

A Good Beginning is a two-and-a-half-year research program, which aims to provide a better understanding of the long-term effects of sit-to-stand desks on sedentary time at school and the relation between sitting time reduction and academic performance, executive functioning, health and wellbeing. The findings may serve as useful information for policy making and practical decision making for school and classroom environments.

**Trial registration:**

The program of “A Good Beginning” is registered at the Netherlands Trial Register (NTR, https://www.trialregister.nl), number NL6166, registration date 24 November 2016.

## Background

Following the advances in technology in the past century, people nowadays spend the largest part of their time awake in a sitting position [1, 2]. In adults, sedentary behavior is associated with serious health risks, such as obesity, cardio-vascular diseases, diabetes, and a reduced cardio-respiratory fitness [3]. Although less consistent than in adults, sedentary behavior is also related to health risks in children [4, 5]. In addition, children’s sedentary behavior is associated with academic under-achievement [4, 5].

Children spend a large part of their waking hours at school sitting [6–8], in a classroom that is designed for sitting. Children’s sedentary behavior, implicitly learned in school, may continue into adolescence [7–11] and adulthood [9, 10, 12]. Consequently, from childhood onwards, sedentary behavior becomes the rule, rather than the exception. Therefore, the school setting, in particular, is the place to reduce children’s sedentary time and promote standing and active behavior, which may also prevent excessive sedentary behavior in later age. Given the fact that the environment has a very strong influence on behavior [13–15], sit-to-stand desks have the potential to invite and seduce children to sit less and to promote standing and active behavior.

On the one hand, reduced sitting time [16–21] and increased energy expenditure [22–24] are relevant physical benefits of using desks that promote standing found in previous studies. On the other hand, concerns about the use of such desks have been expressed by teachers and the long term impact on academic performance is unclear [25]. In short term studies, academic performance didn’t seem to suffer [26]. Moreover, better working memory capabilities [24], and attention and task focus [27] (i.e., the mechanisms suggested to underlie the relation between executive function and academic performance [28]) are advantages that come with the use of desks that promote standing. Hence, academic performance (and cognitive skills) may not suffer from, and even improve with, less sitting and more standing. However, all these benefits have only been reported in short-term studies with a duration of a year or (in most studies, much) less, which may suffer from effects of novelty and season. Students’ enthusiasm to sit less may wane when the novelty of the sit-to-stand desks wears off (cf. [29]), and children are more activity prone in summer than in winter [30].

The program of “A Good Beginning” entails a group-randomized trial in which the merits of sit-to-stand desks in the primary school classroom are investigated over a two-and-a-half-year period, beyond the effect of novelty and controlling for season. To this end, two grade-three groups (students aged 8–9 years) were recruited. In The Netherlands, grade-three students are the oldest students to recruit for a study of this duration. In the final year of primary school, sixth grade, the curricular activities differ notably from the activities in the curriculum of grades one to five. Children in one group, the experimental group, received sit-to-stand desks for the entire study. Students in the control group use regular, seated desks. The results of the program are expected by the beginning of 2020.

The primary aim of the program of “A Good Beginning” is to assess possible harm inflicted on academic performance as an adverse event of long-term implementation of sit-to-stand desks in the primary school classroom. Based on previous findings in shorter term studies [24–27, 31], we expect that the sit-to-stand desks are proper alternatives to regular, seated desks without negative effects on academic performance, and possibly with positive effects. Secondly, in terms of effectiveness, the program aims to assess the long-term effect of sit-to-stand desks on sedentary time. Based on earlier findings, a reduction in sedentary time may be expected.

Furthermore, to gain a broader view on the long term effects, cognitive skills and indicators of health and wellbeing are investigated in relation to sedentary time. Cognitive skills relevant to academic performance, such as working memory, planning, inhibition, and cognitive flexibility, may be influenced by sedentary time [24, 27, 28]. Inactivity and sedentary behavior are negatively associated with wellbeing [32–34], physical fitness [4, 5], and strength [4], and positively associated with childhood obesity [4, 5], (cf. [35]), constipation [36, 37], and a higher risk of insomnia and sleep disturbance [4, 38]. Moreover, short sleep duration and sedentary behavior together are associated with childhood obesity [39], while executive function appears to mediate between sleep duration and sedentary behavior [40].

The outcomes of this study will provide a better understanding of the effects of the classroom environment on academic performance, sedentary time, cognition, health, and wellbeing. The findings may serve as useful information for policy making and practical decision making with regard to school and classroom environments, as well as for future long term efficacy trials on a larger scale. With this study protocol, together with the ethical approval and trial registration, we wish to contribute to transparency, reduce publication bias, and improve reproducibility. This study protocol prevents unnecessary duplication of research, and indicates when to expect the results and findings.

## Methods

The program of “A Good Beginning” has received ethical approval from the Dutch Central Committee on Research Involving Human Subjects (CCMO, https://english.ccmo.nl, number NL60159.000.17). This study is conducted according to the principles of the Declaration of Helsinki [41] and in accordance with the Medical Research Involving Human Subjects Act (WMO) [42]. Risks associated with participation and physical and psychological discomfort are very small to negligible. There are no risks related to the use of sit-stand desks other than, or additional to, the use of regular desks. A SPIRIT checklist covering all recommended trial protocol items is provided as Additional file 1.

### Design

This is a prospective, two-armed, group-randomized trial (see Fig. 1). The trial started in 2017 and will be completed in 2019. Outcomes are assessed at baseline (T0; May 2017) and at five follow-up sessions (T1-T5) with an interval of approximately 6 months, alternately in summer (i.e., July 2017, 2018 and 2019) and winter (i.e., January/February 2018 and 2019) seasons over three academic years. After the baseline assessment, which took place after informed consent, a coin toss (by [name] in the presence of the teachers and the deputy director) determined which group is the experimental group; the other group is the control group. Most tests during the assessment periods take place at school; activity tracking and keeping diaries (also) take place outside the school.

**Fig. 1 Fig1:**
[figure not shown]
Flow-chart of the program of “A Good Beginning”

Blinding is not possible for children, teachers and parents/caregivers. Attempts are taken to keep assessors blinded. However, working with children in this age range proves to be difficult to uphold blindness of assessors. Nevertheless, the influence of assessors on most, and at least on the primary outcomes is considered minimal. The assessors are neither present at the time of measuring sitting time nor at testing academic performance. The assessors are trained junior researchers from Leyden Academy on Vitality and Ageing (Leyden Academy) and the Cognitive Psychology Unit from the Institute of Psychology at Leiden University. Under primary and secondary outcome variables we indicate for which outcome assessment the assessors (and teachers) are present for supervision.

Each year the study is evaluated by the principal investigators, the involved teachers, the school (deputy) director, and members of the Parent-Teacher Association. During this meeting, the progress of the study, as well as safety issues related to testing and the use of the sit-stand desks are discussed.

### Recruitment

Students of two grade-three groups (aged 8–9 years) following regular primary education were recruited from a school in Leiden, The Netherlands, of which the school director initiated this study. At this school there were four grade-three groups. The common group size is 26 to 30 students. The deputy director of the school selected two groups in consultation with the teachers, based on the willingness of the teachers to be involved in the study. All children in both groups were asked to participate. The allocation was only established after baseline assessment (which was after informed consent). In order to be eligible to participate in this study, a student had to meet all of the following criteria:
Follow regular primary education in third gradeHave a signed Informed Consent form to participate; given the age, parents/caregivers should sign the Informed Consent form for their child but the student will be asked to sign one as wellBe physically able to stand without any serious health issues or injuries; note that a student who is normally physically able to stand, but temporarily unable to do so because of a recovery from a temporary injury of trauma, can still participate in this study

Students who object to participate are not included in the study. Examples of objection are (signals of) fear, sadness, and anger. We expected to recruit around 20 students per group. Students who did not participate from the start of the study, but wish to do so at a later moment, are also enrolled at the next moment of testing. Those who terminate their participation before the end of the study are asked for the reason(s) why. Demographics of students that in fact are recruited (and for whom we received written informed consent from themselves and their parents/caregivers) are presented in Table 1.

**Table 1 Tab1:** Participants’ age and sex

	Control group	Intervention group	Total
	(n = 19)	(*n* = 19)	(*n* = 38)
Years of age median [range]	9.0 [8.5 to 10.2]	8.9 [8.5 to 10.3]	8.9 [8.5 to 10.3]
Girls n (%)	10 (52.6)	11 (57.9)	21 (55.3)

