### Intervention

In the experimental classroom, newly developed sit-to-stand desks replaced the regular desks. These sit-to-stand desks are called Adjust-Table Basic, and are manufactured and provided by Presikhaaf Schoolmeubelen, Arnhem, The Netherlands (https://www.schoolmeubelen.com). The desks have been designed to be easy to operate by young children. They are operated by a lever, which releases a gas spring lock. The gas spring allows very low-effort raising and lowering of the desktop. The desktops of the sit-to-stand desks have the same dimensions as the desktops of the regular desks (i.e., 500 × 700 × 18 mm). Height can be infinitely adjusted between 75 and 120 cm.

Each student in the experimental group received such a sit-to-stand desk, also the students that do not participate in the study. They will keep their sit-to-stand desks until they go to secondary school. The teacher of the experimental group also received a sit-to-stand desk (for adults). The students in the experimental group are not obligated to stand; rather, they are invited to stand, first by the mere opportunity to stand offered by the sit-to-stand desks (cf. affordance: the qualities or properties of an object that define its possible uses or make clear how it can or should be used), and second by the teacher who functions as a role model. For instructions, however, the teacher can order all children to sit for a proper view the (digital) blackboard at the front of the classroom. The students in the control group use their regular desks, as does their teacher.

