### Primary outcome variables

Primary outcome measures are academic performance and the proportion of sitting time at school. Academic performance is assessed with the standardized and norm-referenced CITO test battery [43]. The standard procedure for most schools in The Netherlands is to assess academic performance twice each year with the CITO test battery. The scores of arithmetic, orthography, and reading comprehension are used in this study. Academic performance is assessed shortly before the week that sitting time is measured.

Sitting time is measured with an Activ8® Professional activity tracker [44, 45]. The Activ8® Professional (30 × 32 × 10 mm) is a 3D accelerometer that classifies postures and activities when worn on the upper leg: lying, sitting, standing, walking, cycling, and running. As with most other activity trackers, the Activ8® Professional is not able to validly identify all categories [28]. In youths, it can validly distinguish basic postures and activities (i.e., good to excellent validity), but has difficulty in distinguishing standing from other movements in complex activities; in complex activities, standing is often underestimated and detected as walking [44]. Each assessment (i.e., twice each year), an activity tracker is fixed on the upper leg of all participating students with a skin-friendly, waterproof, and transparent dressing (Tegaderm™, 3 M), halfway between the hip and knee. The activity tracker is worn for a school week during each assessment period: 24 h each day for five consecutive days from Monday morning till Friday afternoon. The recording interval is set at 10 s. At the end of the week data are collected via the Activ8® Professional recording tool.

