### Statistical analysis

The statistical analysis will be conducted in SPSS. A two-tailed significance level of .05 will be used for all tests.

Summary statistics for the baseline measures and participant demographics for both groups will first be examined. Dependent on the variable, the means, medians or frequencies will be compared between both groups using a two-sample T-test, a Mann-Whitney U test or chi-square test, as appropriate.

Outcome data obtained from all students will be included in the data analysis, and data will be analyzed as per group allocation. In our statistical analysis the longitudinal and multilevel structure of the data are acknowledged and will be taken into account in achievement growth modeling. For this, mixed modeling will be used, because this specifically allows for the analysis of repeated measures and nested data. Furthermore, missing data are better handled in mixed modeling. We will first determine the growth (longitudinal changes) for the different outcome measures on an individual and on a group level. In determining the proportion of variance explained by group allocation (i.e., sit-to-stand or regular desks) for sitting time as well as for academic performance (i.e., the primary outcome measures), explanatory variables such as age, gender and baseline outcomes will be added to the model. We will do this both on an individual and on a group level, also for a number of secondary outcome measures. We will test for significance of the effect of group allocation on a group level.

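### Children may enrol after the coin toss, knowing their arm, and are pooled with those who consented before it; selection into both primary comparisons is left open for these later entrants

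*Protocol article*

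**What the plan says.** The Recruitment section sets the order of events for the starting cohort: "The allocation was only established after baseline assessment (which was after informed consent". The Design section says the same and dates T0 to May 2017.

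The Recruitment section also opens a second route into the trial: "Students who did not participate from the start of the study, but wish to do so at a later moment, are also enrolled". Entry is at the next test session. The sentence gives no last date and no limit on numbers.

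Three other statements bear on what a later entrant knows and has experienced:

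- Design, text below Fig. 1: "Blinding is not possible for children, teachers and parents/caregivers".
- Intervention: "Each student in the experimental group received such a sit-to-stand desk, also the students that do not participate in the study".
- Primary outcome variables, on the academic scores: "The standard procedure for most schools in The Netherlands is to assess academic performance twice each year with the CITO test battery".

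The Statistical analysis section states the analysis set: "Outcome data obtained from all students will be included in the data analysis, and data will be analyzed as per group allocation". It plans mixed models to which "explanatory variables such as age, gender and baseline outcomes will be added to the model", and remarks: "Furthermore, missing data are better handled in mixed modeling". It does not distinguish children by time of entry.

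**The concern.** In an unblinded trial of two classes, taking consent before the toss is the main protection against selective participation. Children who enrol later do not have that protection. They and their parents know the arm. In the experimental class they have used the desk for weeks or longer before deciding, while non-participants in the control class have had no such experience. The reasons for joining can therefore differ by arm.

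Both primary outcomes are exposed. The first aim is to detect academic harm through a non-inferiority comparison. If children who cope well with the desk join and those who struggle stay out, the experimental mean rises and harm is harder to see. If children who like standing join, the reduction in sitting time looks larger than it is. The documents do not show that selection runs in these directions, but nothing in the stated rules prevents it.

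The baseline adds a second difficulty. Later entrants have no study T0 for tracker-measured sitting time or the study-specific tests. A model with T0 as a covariate would normally omit them, in tension with the statement that all students are included. A model without it keeps them, with the selection uncorrected. The adjusted and unadjusted results would then rest on different children.

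**Working it through.** **1. The plan's own benchmark.** Inputs from the section on sample size, power and non-inferiority: 20 per group; reading SD 25 and mean 159; arithmetic and orthography SD 26 and mean 214.

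- Reading: SE = 25 × √(2/20) = 7.91; half-width = 2 × 7.91 = 15.8; 15.8/159 = 9.9%. This matches the stated 7.9, 15.8 and 10%.
- Arithmetic and orthography: SE = 26 × √(2/20) = 8.22; half-width 16.4, or 7.7% of 214. The stated 8.3, 16.6 and 7.8% are close.
- In SD units the reading half-width is 15.8/25 = 0.632.

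**2. How many could join.** Inputs from Recruitment and Table 1: usual class size 26 to 30; 19 enrolled per group.

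- 26 − 19 = 7, and 7/26 = 27% of the class.
- 30 − 19 = 11, and 11/30 = 37% of the class.

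These are upper bounds. The class size is the school's usual figure, not the recorded size of these two classes, and some non-participants may be ineligible or unwilling.

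**3. Shift in one arm's mean.** If L children join an arm of 19 and differ from the rest by d SD, the unadjusted mean of that arm moves by L/(19 + L) × d. Assume that joining occurs in one arm only and d = 0.5; neither is in the document.

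- L = 4: 4/23 × 0.5 = 0.087 SD, or 0.087 × 25 = 2.2 reading points; 2.2/15.8 = 14%.
- L = 8: 8/27 × 0.5 = 0.148 SD, or 3.7 reading points; 3.7/15.8 = 23% (24% if 0.632 is first rounded to 0.63).

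The text also speaks of about 10% of the mean as the largest acceptable difference. For arithmetic and orthography that is 21.4 points, or 21.4/26 = 0.82 SD. The same shifts are then 0.087/0.82 = 11% and 0.148/0.82 = 18%.

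**4. Range over the assumptions (reading, one arm only).**

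| Late joiners | Share of arm | d = 0.2 | d = 0.5 | d = 0.8 |
|---|---|---|---|---|
| 3 | 14% | 0.7 points (4%) | 1.7 (11%) | 2.7 (17%) |
| 7 | 27% | 1.3 (9%) | 3.4 (21%) | 5.4 (34%) |
| 11 | 37% | 1.8 (12%) | 4.6 (29%) | 7.3 (46%) |

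Percentages in the last three columns are of 15.8. The shift applies only at visits where the late joiners are measured.

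**5. Effect of the model.** A simulation assumed no true effect, a baseline correlation of 0.7 and d = 0.5. With everyone kept and no baseline term, the mean bias was 1.7, 3.3 and 4.6 points for 3, 7 and 11 late joiners, in line with step 4. With T0 as a covariate and children without it dropped, the bias was about zero, because only the starting children remained. Whether the bias enters thus depends on a choice that the article leaves open.

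**The case against.** The strongest reply has four parts.

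- **Concealment.** A reader might infer that late entry undoes allocation concealment for the whole trial. The documents do not support this. Consent and T0 preceded the toss for the starting cohort, and late entry cannot alter the toss. Nor does it change exposure, because the desk follows class membership whether or not a child is enrolled. What remains is selective measurement of later entrants.
- **Baseline.** It is tempting to say that later entrants have no baseline at all. That is secure for sitting time and the study-specific tests. For academic performance a pre-allocation CITO score may be in school records, although the article does not say that it would be used.
- **Model.** Saying that late entry breaks the baseline-adjusted model goes too far. The article does not fix T0 as a covariate with deletion of incomplete cases, and a condensed article may leave the handling of a missing T0 to a fuller plan. The two harms also exclude each other within one model: late joiners are either dropped, with little bias, or kept, with no conflict over who is included. This stands. It does not settle which of the two the primary result will be.
- **Size.** No late joiner is documented. Joining in one arm only and a uniform advantage are assumptions. If nearly all non-participants in both classes joined, selection would shrink. The third-grade criterion, read literally, would leave little room for entry after July 2017. However, the late-entry sentence carries no such limit, and the two statements are not reconciled.

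These points narrow the concern. They do not answer its core, which rests on stated rules: entry stays open after an unblinded allocation, and the analysis set takes in everyone without distinction.

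**Conclusion.** The point holds in a limited form. Children who consented before the toss keep the protection of concealment; later entrants do not, and the stated analysis set mixes the two. Arm-dependent selection could therefore enter both the non-inferiority and the sitting-time comparisons.

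The actual bias is unknown and may be small, since neither the number nor the characteristics of late joiners are given. The 14 to 23% figure is an illustration for reading only, conditional on 4 to 8 joiners in one arm with a 0.5 SD advantage. It is smaller (11 to 18%) against 10% of the mean for arithmetic and orthography. With about 19 children per arm, even a handful of entrants is a noticeable share. This should be corrected, but it does not invalidate the comparison among the starting children.

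**What to change.** - Define the primary analysis set for both primary outcomes as the children who consented before the coin toss. Do not define it as the 38 in Table 1 with T0 data, because the table does not show that all 38 have a T0 measurement.
- Report late joiners by arm and by visit of entry.
- Include late joiners only in a sensitivity analysis.
- State one rule for a missing T0, covering late joiners and any starting child without it, and say whether an earlier school CITO score may serve as the academic baseline.
- If T0 is modelled as one of the repeated outcomes, give each class its own T0 mean. A common baseline mean is not justified with two intact classes and a single toss.
- Reconcile the late-entry sentence with the third-grade criterion.

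The cost is a change of wording, a small table and one extra model run. The downside is that a few late children are left out of the primary analysis.
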